## Introduction

Chronic obstructive pulmonary disease (COPD) is a major cause of morbidity and the fifth leading cause of mortality worldwide [Siafakas 1995, Postma 1998]. The WHO organisation has foreseen that COPD mortality will be at the third ranking, after cancer and cardiovascular mortality, by the year 2020. This calls for adequate intervention in the progression of disease and, above all, a better understanding of the pathogenesis and pathophysiology of COPD.

Current knowledge shows that the disease is characterized by progressive and largely irreversible airways obstruction [Postma 1998]. This is demonstrated by an accelerated decline with age of FEV1 (forced expiratory volume in 1 second), associated with symptoms of dyspnoea at rest or on exertion. The disease leads to impaired quality of life, disablement and eventually death. The pathogenesis of COPD is closely associated with cigarette smoking. Risk factors for the development of COPD in smokers are continuation of smoking, low FEV1, and increased airway hyperresponsiveness [Tashkin 1996]. Furthermore, it has recently been reported that elevated serum IgE and peripheral blood eosinophilia are associated with a more rapid decline of FEV1 in smokers [Villar 1995]. It appears that the susceptibility, development, clinical course and prognosis of COPD are at least partly determined by host characteristics.

The pathology of COPD is heterogeneous [Saetta 1994, Postma 1998]. It can include (acute and chronic) inflammation within the small airways as well as features of emphysema. The bronchiolar and peribronchiolar inflammation in smokers with COPD is characterized by *e.g.* increased numbers of epithelial mast cells and macrophages [Grashoff 1997], elevated numbers of neutrophils and of CD3+ T lymphocytes with an increase in the CD8+ subset [Saetta 1998], and increased expression of growth factors, such as TGFβ (transforming growth factor beta) [de Boer 1998]. It is important to notice that some of these pathological features can be confirmed in bronchial biopsy specimens as obtained from the large airways [O'Shaughnessy 1997]. The current working hypothesis is that this inflammatory response not only leads to swelling and structural changes of the airway walls (fibrosis, smooth muscle growth) [Saetta 1998], but also to destruction of peribronchiolar alveolar attachments and parenchymal destruction by an imbalance of local proteases (such as neutrophil elastase) and their inhibitors (such as SLPI) [Thurlbeck 1990]. As this imbalance and the resulting destruction are not completely explaining the development of emphysema, it can be postulated that qualitative or quantitative defects in local tissue repair are also important in COPD

(emphysema) patients. Tissue repair as a form of wound healing is regarded as an inflammatory process, in which inflammatory cells play a major regulating role. Consequently, long-term anti-inflammatory therapy can be expected to reduce not only damaging inflammation, but also the local tissue repair process [Timens 1997].

months remained unaltered. This is indicative of transient benefits of inhaled steroids in COPD, predominantly during the first months of treatment. Using oral steroid therapy in COPD it has been shown that the greatest response occurs in those patients with eosinophilic inflammation within the airways. This suggests that steroids might reduce some of the features of acute airways inflammation in COPD, whereas they may not influence the structural changes within the airways. As indicated above, it may even be postulated that steroids can have deleterious effects on chronic inflammation [Timens 1997], e.g. by limiting neutrophil apoptosis or stimulation of collagen production [Gauldie 1997].

Taken together, it appears that inhaled steroid treatment in COPD has only transient effects on functional outcome. The reasons for this are unknown, but need to be examined at the level of airway pathology. Therefore, we aim to investigate the clinical, functional as well as pathological outcome of short- and long-term treatment with inhaled steroids in patients with COPD. This will clarify whether short-term inhaled steroid treatment will suffice, or whether long-term treatment is still required to preserve the clinical, functional and/or pathological benefits. Since add-on therapy by long-acting  $\beta_2$ -agonists in combination with inhaled steroids has been demonstrated to be highly effective in asthma [Woolcock 1996, Pauwels 1998], we will also examine the short- and long-term benefits of such combination therapy in COPD. Short-term studies suggest that long-acting  $\beta_2$ -agonists may improve symptoms, quality of life, and exercise tolerance in COPD. However, this has not been formally addressed in longitudinal studies, nor in the presence of inhaled corticosteroids.

## Hypothesis

We hypothesize that inhaled steroid treatment in patients with COPD leads to the following:

1. An initial improvement in symptoms, quality of life, and FEV1, associated with a reduction in features of airways inflammation.
2. 6 Months of treatment will be sufficient to maintain these initial effects; continuation of therapy beyond 6 months will lead to an unfavourable balance between destruction and repair within the airway wall.
3. After the initial improvement, the increased annual decline in FEV1 continues, which is associated with on-going airway remodelling and parenchymal destruction.
4. Airway hyperresponsiveness, elevated serum IgE, Th2 cytokine profile, and eosinophil infiltration are predictive of the initial benefits on symptoms, FEV1, and airway inflammation.
5. Addition of a long-acting  $\beta$ 2-agonist to inhaled steroid treatment augments the benefit of therapy with regard to symptoms and quality of life, without changing the decline in FEV1 or the pathological outcome.

## Aim

The aim of the present study is to test the above hypotheses by comparing the clinical, functional and pathological benefits of:

- short-term (6 months) inhaled fluticasone followed by placebo (24 months)
- long-term (30 months) inhaled fluticasone
- long-term (30 months) salmeterol + inhaled fluticasone
- long-term (30 months) placebo

in a double blind, randomised, controlled trial in patients with COPD.

## **Outcome parameters**

### Primary

#### Inflammation

- localisation, numbers and profile of neutrophils, eosinophils, macrophages, and CD8+ T cells in bronchial biopsy specimens

### Secondary

#### Clinical

- symptoms, exacerbation rate, health-related quality of life, level and decline in FEV1
- 6 minutes waling distance

#### Inflammation

- cellular and soluble markers in BAL and induced sputum
- profile of bronchial epithelial cells in bronchial biopsies
- markers of airway remodelling in bronchial biopsies

#### Pharmaco-economics

- cost-effectiveness
- cost-utility

### Tertiary

#### Functional

- airway responsiveness (PC20) to methacholine

#### Inflammation

- expression and localisation of pro- and anti-inflammatory cytokines or mediators in bronchial biopsies

## **Patient selection**

### *Patient recruitment Groningen*

Patients with COPD (n=135) will be selected from the practices of general practitioners and in the outpatient clinics of the Departments of Pulmonology from the University Hospital Groningen and the Leiden University Medical Center, and by advertisement through the media.

Participating general practitioners will be asked to select patients with COPD, who have not been treated with regular inhaled or oral corticosteroid during the last six months. In order to find these patients they will select patients between 45 and 75 years with a history of at least 10 pack years of smoking and at least one of the following symptoms: chronic cough, chronic sputum production, frequent exacerbations, or dyspnoea on exertion (see detailed inclusion and exclusion criteria, as listed below).

When selected the patient will be asked to cooperate in the study, and they will receive the patient information sheet. If in principle the patient is willing to cooperate, he or she will be referred to one of the study investigators. The study investigator will perform spirometry (FEV1) in the investigational laboratory or at the home of the patient, and will provide detailed information to the patients about the study.

When the patient fulfils all the inclusion criteria and none of the exclusion criteria, informed consent must be signed by the patient and an appointment for visit one will be made.

### *Patient recruitment Leiden*

In Leiden patients with COPD (n=135) will be recruited by advertisement through the media (appendix). Volunteers responding to this advertisement will first be screened by a telephone questionnaire taken by the investigators. When patients meet most of the inclusion criteria and if (in principle) they are willing to participate, they will be asked to visit the hospital to perform spirometry. Subsequently, when FEV1 fulfills the inclusion criteria, the study investigator will provide information to the patient about the study, show a video demonstrating a bronchoscopy procedure and give the patient information form (appendix). One week later the investigator will telephone the patient and ask if he or she is willing to participate. If so, the study investigator will make an appointment for the first visit.

On this first visit the patient and investigator or his/her designee have to sign and date the general informed consent for participation in the study and an informed consent

concerning the three bronchoscopies (appendix).

After the first bronchoscopy the patient will be asked to complete a questionnaire about his or her experiences with this procedure. After having completed this questionnaire the patient will be asked specifically if he or she is still willing to participate in the study (appendix). If this is the case and the patient fulfills all the inclusion criteria and none of the exclusion criteria, the patient will be randomised and the next visit will be planned.

### *Inclusion criteria*

1. Age: 45-75 years
2.  $\geq 10$  packyears of smoking
3. At least one of the following symptoms: chronic cough, chronic sputum production, frequent exacerbations, or dyspnoea on exertion
4. No course of oral corticosteroids during last 3 months, no maintenance treatment with inhaled or oral steroids during last 6 months
5. postbronchodilator value (after 400  $\mu$ g of inhaled salbutamol) of FEV1 below the 90% confidence interval (90% CI) of the predicted FEV1, and postbronchodilator FEV1/IVC ratio below the 90% CI of the predicted FEV1/IVC ratio [Quanjer 1993]
6. postbronchodilator FEV1 > 1.3 litre and > 20% of predicted value.
7. Written informed consent

### *Exclusion criteria*

1. Prior or concomitant history of asthma
2. Alpha-1 antitrypsin deficiency (SZ, ZZ, zero phenotype)
3. Other active lung disease except for mild bronchiectasis; bronchiectasis should not be the main reason for chronic cough and/or sputum production with additional mild obstruction.
4. Contra-indications for elective bronchoscopy, such as O2 saturation <90%, abnormal coagulability, anti-coagulant therapy which cannot be temporarily withheld for performance of bronchoscopy, history of pneumothorax, uncontrolled angina pectoris.
5. Other diseases likely to interfere with the purpose of the study.
6. Inability to keep diary and to understand written and oral instructions in Dutch.

## Study design

In this prospective, longitudinal, double blind study COPD patients will be followed up for 2.5 years (see *figure*). The study begins as a 3 groups parallel design during 6 months, followed by a 4 groups parallel design during 24 months. The aim is to finish the study with 50 patients in each of the 4 parallel groups at 30 months.

Patients will be treated by the investigator-physician with inhaled corticosteroids (500 µg b.i.d. fluticasone by DiscusR), or inhaled corticosteroids with long-acting  $\beta_2$ -agonist (+ 50 µg b.i.d. salmeterol), or a matching placebo for the first 6 months. Thereafter, half of the corticosteroid group will continue and the other half will receive placebo for 2 years. The patients who will be treated with placebo or inhaled corticosteroids + salmeterol continue their treatment during the complete period of 2.5 years. Rescue treatment will be on demand usage of inhaled inpratropium bromide, which is a standard bronchodilator in COPD [Siafakas 1995].

Subjects who fulfil all inclusion criteria and none of the exclusion criteria (see patient selection) will be allocated to receive placebo, inhaled corticosteroids (equivalents of 500 µg b.i.d. = 1000 µg fluticasone) or inhaled corticosteroids + salmeterol at the beginning of the study using the minimization method. The use of minimization will provide treatment groups that are closely balanced for a number of variables (centre, gender, current smoker, FEV1/IVC < 60%, PC20 methacholine < 2 mg/ml), which might influence the primary and secondary outcome variables [Altman 1995]. The first patient is given a treatment at random. For each subsequent patient we will determine which treatment will lead to better balance between the groups with respect to centre, gender, smoking, FEV1/IVC and PC20. The group with inhaled steroid will be randomly allocated to either the steroid group or the placebo group after 6 months of steroid treatment. Minimization will be performed using a computerized method [Pocock 1983].

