#### *Number of patients*

In order to achieve a total number of  $n=200$  ( $n=50$  per treatment arm) at the end of the study, we will initially include 270 patients.

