## Data analyses

### *Determination of the sample size*

The determination of the sample size is based on detectable differences in the primary outcome variables, the mean inflammatory cell counts in bronchial biopsies between the different treatment groups. Under the assumption that the distributions of (logtransformed) cell counts is approximately normal and the standard deviation in the different treatment groups is approximately equal, the sample size follows:

A sample size of 8-25 patients is needed to detect at least one doubling difference in mean cell number per  $0.1\text{mm}^2$  for a particular inflammatory cell to detect changes within a group ( $\alpha=0.05$ ,  $\text{power}=0.80$ ). A sample size of 13-48 subjects per group is required to detect at least 1 doubling difference in cell number between parallel groups [Sont 1997].

Based on an estimated standard deviation of repeated cell counts in bronchial biopsies of 2.34 fold change, a sample size of 50 per study arm allows us to detect at least a 1.62 fold different increase in number of inflammatory cells/ $0.1\text{ mm}^2$  between two groups.

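### The entry minimisation carries no allocation ratio; run unweighted over three groups, it cannot deliver the planned 50 completers in each fluticasone arm from 270 patients.

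*Protocol*

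**What the plan says.** Under Study design, the protocol describes the structure as follows: "The study begins as a 3 groups parallel design during 6 months, followed by a 4 groups parallel design during 24 months". At entry each patient goes to placebo, fluticasone, or fluticasone plus salmeterol. The first allocation is random. After that, "For each subsequent patient we will determine which treatment will lead to better balance between the groups", judged on centre, gender, smoking, FEV1/IVC and PC20. No target ratio or weight for the three treatments appears in the text.

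The fourth arm arises later by splitting one of the three: "Thereafter, half of the corticosteroid group will continue and the other half will receive placebo for 2 years". This second step is a random allocation made after 6 months of steroid treatment.

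The size targets are set for the four final arms. Study design states: "The aim is to finish the study with 50 patients in each of the 4 parallel groups at 30 months". The Number of patients section plans for 200 completers, and to have them "at the end of the study, we will initially include 270 patients". Determination of the sample size ties the detectable effect to the same number: "a sample size of 50 per study arm allows us to detect at least a 1.62 fold different increase in number".

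**The concern.** The allocation rule works on three groups and the size target on four. Ending with 50 in each half of a group that is later split requires that group to be twice as large as the others from the start. Minimisation without weights pulls the other way: by evening out the counts at each level of each factor, it also evens out the group totals. Someone who programs the rule exactly as described would build a trial with too few patients in the two fluticasone arms and a surplus in placebo and combination.

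The shortage falls on the contrast between 6 and 30 months of fluticasone. That contrast tests the second hypothesis, and the Introduction presents it as a question the trial will settle. The ratio acts from the first patient onward, so an analysis plan cannot repair it afterwards.

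**Working it through.** **Inputs.**
- Enrolled: 270; completers: 200, as four arms of 50 (Number of patients; Study design).
- Retention: 200/270 = 74.1%. This is derived, since no dropout rate is stated, and is assumed equal across groups.
- SD: 2.34-fold, so ln 2.34 = 0.850. Planned difference: 1.62-fold, so ln 1.62 = 0.482 (Determination of the sample size).
- Alpha 0.05 and power 0.80. These stand beside the one-doubling calculation in the same section. I assume that they carry over to the 1.62-fold figure and that the test is two-sided.

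**Step 1: reproduce the plan's figure.** For a two-sample comparison of log counts, the detectable fold difference is approximately exp[(1.960 + 0.842) × SD × √(1/n₁ + 1/n₂)]. With 50 v 50: exp(2.802 × 0.850 × 0.200) = 1.61. The noncentral t gives 1.618, which rounds to the stated 1.62, with power 80.2% for 1.62-fold. The figure is correct for 50 per arm. The results in step 4 use the noncentral t.

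**Step 2: group sizes under the rule as written.** Simulating unweighted minimisation on five two-level factors with assumed prevalences (N = 270, 30 runs) gave mean group sizes of 90.2, 89.8 and 89.9. So 270/3 = 90 per entry group, and each fluticasone half has 90/2 = 45. Since 45 < 50, the target is out of reach with no dropout at all.

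**Step 3: completers at equal retention.**
- Placebo and combination: 90 × 200/270 = 66.7 each.
- Each fluticasone half: 45 × 200/270 = 33.3.

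**Step 4: consequences at 30 months.**

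| Contrast | n v n | Power for 1.62-fold | Detectable at 80% |
|---|---|---|---|
| As planned | 50 v 50 | 80% | 1.62-fold |
| Stop v continue | 33.3 v 33.3 | 62.6% (62.2% at 33 v 33) | 1.81-fold |
| Stop v continue, no dropout | 45 v 45 | 75.9% | 1.66-fold |
| Fluticasone half v placebo or combination | 33.3 v 66.7 | 75% | 1.67-fold |
| Placebo v combination | 66.7 v 66.7 | 90% | 1.52-fold |

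**Step 5: contrasts at 6 months.** Fluticasone is still one group. Using the same retention as a conservative figure, equal allocation gives 66.7 v 66.7, with 1/66.7 + 1/66.7 = 0.030. A 1:2:1 allocation gives 100 v 50, with 1/100 + 1/50 = 0.030. The precision is the same, and power for 1.62-fold is about 90% either way.

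**Step 6: with a 1:2:1 target.** Enrolment is 67.5/135/67.5. Multiplying by 200/270 gives 50/100/50 completers, and halving the 100 gives 50 in each of four arms. The same simulation weighted 1:2:1 gave means of 67.5, 135.1 and 67.4. Keeping equal groups and still reaching 50 per half would take 3 × 2 × 50 × 270/200 = 405 patients.

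**The case against.** The protocol never says 1:1:1. Its stated aim for the minimisation is balance on prognostic variables, which can be achieved at 1:2:1 as well as at 1:1:1. Its only numerical targets, four arms of 50 and 200 completers from 270, fit 1:2:1 exactly, and on that reading there is no shortfall. The design figure is not shown here and may give group sizes; the program for the computerised method may contain weights. A simulation coded with equal weights shows what unweighted minimisation does, not that this trial will use it.

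Most of this stands. A reader might infer that the plan fixes equal groups and that 33 completers and 62% power are settled results. The text does not support that: both figures depend on unweighted minimisation and on equal dropout, and the 74% retention is itself derived. A reader might also infer that the 1.62-fold figure fails for every contrast involving fluticasone. That is wrong for the 6-month comparisons, which use the undivided group, and the loss against placebo or combination at 30 months is modest.

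The mismatch itself remains. The targets need a double-sized fluticasone group, and the only procedure described, followed literally, does not produce one. If the figure or the program gives the intended ratio, the text of Study design still has to agree with it.

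**Conclusion.** The concern holds in conditional form. The entry ratio is unstated. The allocation procedure as written, run without weights, cannot produce the stated final arm sizes from 270 patients: each fluticasone half starts with at most 45. That part needs no assumption about retention. With equal retention of 200/270, the halves end at about 33 each. The 30-month stop-versus-continue contrast then has about 62% power for 1.62-fold and can detect about 1.81-fold, while a fluticasone half against placebo or combination has about 75% power and can detect 1.67-fold. These figures use the protocol's own SD with two-sided alpha 0.05. The 1.62-fold calculation at 50 per arm is itself sound. The most likely intention is 1:2:1, which would remove the shortfall, but the protocol has to say so.

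**What to change.** In Study design, state that placebo : fluticasone : combination is allocated 1:2:1, and say how the minimisation respects it. Either compare the factor-level counts after dividing them by the target weights, or minimise over the four final arms at entry, with the two fluticasone arms treated identically until month 6; the sentence on the month-6 random split would then be reworded to match. The result is about 67.5/135/67.5 enrolled and 50 completers per arm, with about 80% power for 1.62-fold. The cost is one sentence and one weight in the allocation program before the first patient, with no extra patients.

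If equal allocation to the three entry groups is really meant, restate the expected completers per arm in Study design and Number of patients (about 67, 33, 33 and 67). In Determination of the sample size, restate the detectable difference by contrast (about 1.81-fold for stop versus continue and 1.67-fold for a fluticasone half versus placebo or combination). The alternative is to raise the total to about 405.

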## Measurements

Measurements of symptoms, QOL, and spirometry (postbronchodilator) will be made every 3 months. In addition, exhaled nitric oxide (NO), bodyplethysmography and carbon-monoxide diffusion capacity will be measured at 0, 6 and 30 months. Bronchial biopsies, bronchoalveolar lavage, and sputum induction will also be performed at 0, 6 and 30 months. Peripheral blood eosinophils, IgE, and PC20 methacholine at 0, 6 and 30 months. In bronchial biopsies,

bronchoalveolar lavage and sputum special attention will be paid to the number of lymphocytes, neutrophils, eosinophils, macrophages, mast cells, and the state of activation of these cells and the epithelium.

Once during the study a spiral computed tomography (CT-scan) will be performed to quantify the presence of pulmonary emphysema in each patient [Gevenois 1996], and EDTA-anti-coagulated whole blood will be collected for DNA-isolation, for future studies on gene polymorphisms possibly associated with glucocorticoid responsiveness or other study outcomes.

The effects of treatment will be analysed by relating the observed changes in clinical and pathophysiological outcome, to those in cellular and histological outcome (see analysis).

